Hypotension (lasting >2 hours) and hypovolaemia occurred three times more frequently in the hypothermia group. Bradycardia associated with hypotension also occurred four times more frequently in this group, electrolyte disorders and hyperglycaemia were also found more frequently in the hypothermia group [9]. All of these complications are known side effects of hypothermia. Most are easily preventable with good intensive care and should not be regarded as inevitable consequences of hypothermia treatment. Since even very brief episodes of hypotension or hypovolaemia can adversely affect outcome in TBI, these and other issues may have significantly affected the results of this trial [29-31]. One possible problem was that some of the participating centres had little or no previous experience in using hypothermia. Large centres, familiar with cooling, showed apparently favourable neurological outcomes whereas smaller centres showed poor outcomes.

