#### Other

• 6 month mortality rate

• ICP control

• Incidence of pneumonia across both groups

• Length of stay in the ICU and hospital

• Modified Oxford Handicap Scale score at one month, discharge from the randomising hospital or death, whichever occurs first

• Correlation between the predicted outcome using the modified Oxford handicap scale at hospital discharge and the GOSE Score at 6 months post injury

• Health economics (dependent on additional external funding).

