#### Treatment Allocation

It is not possible to blind local investigators to allocation as it is obvious clinically which patients are receiving hypothermia e.g. equipment required, patient temperature, blood results, fluid requirements. Blinding of outcome data assessment is however be ensured as the GOSE questionnaire is posted to participants by the coordinating centre.

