#### Premature Withdrawal

Participation in any research trial is voluntary and therefore the participant or their legal representative may wish to withdraw from the trial at any point. If this is the case, it should be made clear on a Premature Withdrawal Form whether any previously collected data may still be used for the analysis and which part of the trial the patient is being withdrawn from:

1)Withdraw entirely - the hypothermia intervention is safely terminated, no further data is collected and previous data collected will not be used in the analysis.

2)Withdraw entirely - no further data is collected and the intervention is safely terminated but data previously collected may be used in the analysis.

3)Withdraw from the intervention but be willing to be followed up.

4)Withdraw from being followed up only.

If the patient wishes to withdraw from the trial or their legal representative wishes to withdraw them, they are free to do so without giving a reason and without the patient's medical care or legal rights being affected [47]. If however the patient is withdrawn from the study by the doctor in charge of their care on medical grounds, the reason for this withdrawal must be clearly documented in the data collection form and a serious adverse event form completed if appropriate.

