### Adverse Events

The ***only ***serious adverse events to be collected are:

• Bleeding - defined as a new haemorrhage requiring ≥2 units of packed red cells.

• Cardiovascular instability - defined as a systolic blood pressure <90 mmHg for ≥30 minutes [37]. Terminal hypotension is not be collected.

• Thermal burns >5% of body surface area using the Lund-Browder Chart.

• CPP < 50 mmHg for ≥15 minutes.

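### Hypotension labelled terminal is left out of the cardiovascular-instability event without a definition in the article, so the fatal part of that event can be missing, possibly unequally by arm

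*Protocol article*

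**What the plan says.** The Adverse Events section of the protocol article restricts collected serious adverse events to four types: bleeding, cardiovascular instability, thermal burns and low cerebral perfusion pressure (CPP). Death is not one of them. The second type is "Cardiovascular instability - defined as a systolic blood pressure <90 mmHg for ≥30 minutes", followed directly by "Terminal hypotension is not be collected". The article gives no definition of terminal, no interval before death, and no statement of who makes the call. The low-CPP event, "CPP < 50 mmHg for ≥15 minutes", carries no such exclusion.

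On blinding, the Treatment Allocation section says "It is not possible to blind local investigators to allocation as it is obvious clinically which patients are receiving hypothermia". The only blinding it describes is for the posted GOSE questionnaire. The one place that mentions completing an adverse event form is Premature Withdrawal, which covers patients taken out of the study by their doctor for clinical reasons and states: "the reason for this withdrawal must be clearly documented in the data collection form and a serious adverse event form completed if appropriate".

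The Background (Review of Clinical Evidence) reports of one of the two largest earlier multi-centre trials that "Hypotension (lasting >2 hours) and hypovolaemia occurred three times more frequently in the hypothermia group". It adds a reason for caring: "Since even very brief episodes of hypotension or hypovolaemia can adversely affect outcome in TBI". Deaths are counted separately, since "6 month mortality rate" is among the other endpoints.

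**The concern.** The threshold is objective, but the exclusion is not. An episode can be terminal only in relation to a death that has happened or is expected, so the safety event is conditioned on something that occurs after randomisation and that treatment may influence. Hypotension brought on by cooling that ends in death could be given the label, and so could the final pressure fall of a patient dying from the brain injury.

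Two routes lead to imbalance. Unblinded sites may use the label differently by arm. Or, with identical labelling habits, hypothermia may cause more fatal hypotension, and the rule then removes that excess. The second route needs no bias in anyone's judgement.

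This is a collection rule, so no later analysis plan can restore episodes that were never recorded. The label must also be applied across at least 70 hospitals, and routine monitoring visits with source data verification go only to sites with more than 10 patients (Study Monitoring). At stake is the hypotension comparison, for a complication the Background describes as a known and mostly preventable side effect of cooling.

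**Working it through.** **Is there a figure to reproduce?** No. The article gives no expected rate of cardiovascular instability and no share of episodes expected to be terminal. Every rate and share below is an assumption.

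**Formula.** Let p_C and p_H be the true proportions of patients with an episode meeting the threshold in the control and hypothermia arms. Let t_C and t_H be the shares labelled terminal. Then

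recorded RR = [p_H × (1 − t_H)] / [p_C × (1 − t_C)] = true RR × (1 − t_H)/(1 − t_C).

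The bias depends only on the ratio of the retained shares:

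- t_C = t_H = 30%: factor 0.70/0.70 = 1.00
- t_C = 30%, t_H = 50%: factor 0.50/0.70 = 0.71
- t_C = 30%, t_H = 60%: factor 0.40/0.70 = 0.57
- t_C = 50%, t_H = 30%: factor 0.70/0.50 = 1.40, so a higher share in control would exaggerate the harm

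**Results with t_C fixed at 30%.**

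| Assumed true rates (control, hypothermia) | True RR | t_H = 30% | t_H = 50% | t_H = 60% |
|---|---|---|---|---|
| 5%, 15% | 3.0 | 10.5/3.5 = 3.0 | 7.5/3.5 = 2.14 | 6.0/3.5 = 1.71 |
| 5%, 10% | 2.0 | 7.0/3.5 = 2.0 | 5.0/3.5 = 1.43 | 4.0/3.5 = 1.14 |
| 10%, 15% | 1.5 | 10.5/7.0 = 1.5 | 7.5/7.0 = 1.07 | 6.0/7.0 = 0.86 |

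The first row uses a threefold ratio only because the Background reports that ratio for an earlier trial, which defined hypotension as lasting more than 2 hours.

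**Effect on detection.** For the middle row with the planned 900 per group, power of a two-sided 5% comparison is 98% if all episodes are recorded. It is 92% with equal 30% shares and 35% with 30% versus 50%. Equal labelling costs events but leaves the RR intact; unequal labelling can hide the difference.

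**Does the low-CPP event cover the gap?** CPP is mean arterial pressure minus ICP. Assume a pressure of 90/60 mmHg, so the mean is 60 + 30/3 = 70.

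- ICP 20 mmHg: CPP = 50, on the boundary
- ICP 25 mmHg: CPP = 45, captured
- ICP 15 mmHg: CPP = 55, not captured

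Capture depends on ICP and needs a monitor in place. The Background says ICP fell during cooling in all the high-ICP studies. At the same low blood pressure, a cooled patient with a lower ICP would be less likely to trigger this event, so the backup may itself differ by arm.

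**The case against.** The strongest case for the plan has five parts.

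- **Deaths are not lost.** Six-month mortality is an endpoint, death is part of the GOSE outcome, vital status is checked with the family doctor, and the monitoring committee considers morbidity and mortality and may request further analyses. A reader might infer that fatal hypotension vanishes from the safety data altogether. The documents do not support that: the death is counted, and some episodes will appear under low CPP. The part of the concern that survives is narrower: the fatal part of one event, and its link to hypotension.
- **The mechanism is inferred.** A reader might also infer that unblinded investigators strike out episodes after the patient has died. The article names neither the person nor the time. That sites apply the label is likely, because sites hold the data, but it is not stated. The ordinary meaning of the term is the final pressure fall in a dying patient, not any hypotension followed by death.
- **The full protocol may define the term.** This is fair, and the absence of a definition from a condensed article would not be a finding by itself. But the article states outright that the episodes are not collected. A definition would make labelling more consistent without recovering what it excludes.
- **The exclusion has a purpose.** Agonal hypotension precedes many deaths and can swamp a real difference. With assumed rates of 12% versus 7% and a further 20% agonal episodes in each arm, the RR falls from 12/7 = 1.71 to 32/27 = 1.19. This stands as an argument against simply counting everything, which is why episodes should be flagged and reported both ways.
- **A withdrawal decision is also made by unblinded staff.** True, so a dated flag does not remove all scope for difference between arms. It makes the classification visible and keeps the flagged episodes available for analysis.

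**Conclusion.** The concern holds in a limited form. The rule can remove fatal hypotensive episodes from the cardiovascular-instability count through a label that the article leaves undefined and that depends on actual or expected death. The removal could be unequal between arms, for a harm that the document itself associates with hypothermia.

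The size cannot be determined from the document. The relative risk is unbiased when the share labelled terminal is equal in both arms. It is attenuated when that share is higher with hypothermia and exaggerated when it is higher in control. The illustrative fall from 2.0 to 1.4 rests wholly on assumed shares of 30% and 50%; nothing shows that such a difference would occur.

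Mortality, the GOSE, the primary analysis and the sample size are untouched. Severity is low to moderate.

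**What to change.** Record every episode with systolic pressure below 90 mmHg for 30 minutes or longer. In place of non-collection, flag episodes that start after a dated, documented decision to withdraw life-sustaining treatment or after confirmed brain death. Enter that date on the event form, and report cardiovascular instability by arm with and without the flagged episodes, both to the monitoring committee and in the final report.

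This keeps the aim of setting agonal hypotension aside and allows the effect of doing so to be checked. It changes what is recorded, not how patients are treated.

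The cost is a revised event definition, one date field, more forms for dying patients, and higher raw counts in both arms. Episodes already left uncollected would be recoverable only where site records allow.

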### Trial Management and oversight arrangements

#### Project Management Group

The trial will be coordinated by a project management group, consisting of the grant-holder and Chief Investigator in Edinburgh, Trial Managers and advisers.

#### Trial Management

The trial office is associated with the Edinburgh Clinical Trials Unit in the University of Edinburgh and gives day to day support to the clinical centres. Trial office staff are responsible for all aspects of trial management. These responsibilities include providing research advice and support to all centres, ensuring the timely completion of CRFs in collaboration with all centres, data checking and analysis. The trial office staff are also be responsible for the production of progress reports for the data and safety monitoring committee (DSMC), trial steering committee (TSC), ethics committees and the European Society of Intensive Care Medicine (ESICM) who are funding the study. Publication and dissemination of the study results will be coordinated by the Edinburgh Clinical Trials Unit in collaboration with the Chief Investigator and Principle Investigators.

A senior Trial Manager oversees the study and is accountable to the Chief Investigator. Two Trial Managers supervise the day to day conduct of the trial, including: initiation of trial centres, ensuring training records are maintained and updated, supervision and support of all trial staff, site visits to all participating centres, regularly liaising with all trial investigators, monitoring of centres and site closures. The Secretary/Data Clerk is responsible for all administrative responsibilities of the trial, including: manual data entering from paper CRFs, monitoring response to follow up questionnaires, following up missing data queries and non responses to questionnaires with the local investigators.

The statistical and scientific integrity of a major clinical trial is enhanced by incorporating three distinct statistician roles: the Study Statistician who undertakes all statistical tasks including formal analysis and reporting of data, the DSMC and an Independent Statistician. This Statistician is truly independent having no trial involvement except producing unblinded interim reports for the DSMC at specified time periods.

Subject to additional funding being obtained, a health economist is responsible for the development of the data collection forms required for the economic evaluation, the analysis of economic data and the preparation of the economic evaluation component of the final report.

An IT programmer has established a database management system for efficient conduct of the trial including the randomisation, timely despatch of questionnaires, automatic form monitoring, data validation and cleaning.

#### Trial Steering Committee

The TSC oversees the conduct and progress of the trial. Other members of the trial management group may attend as observers at the invitation of the Chair of the steering committee.

#### Data and Safety Monitoring Committee

An independent DSMC has been established to oversee the safety of the trial participants. During the period of recruitment to the trial, interim analyses will be supplied, in strictest confidence, to the DSMC together with any other analyses that the committee may request.

In the light of these analyses, the DSMC will inform the TSC if, in the opinion of the committee, the randomised comparison in the trial has provided either:

a) proof beyond reasonable doubt that for all or some types of patients, the intervention is clearly indicated.(or contraindicated) in terms of a net reduction in morbidity and mortality across groups. (Appropriate criteria for proof beyond reasonable doubt cannot be specified precisely. A difference of at least three standard deviations in the interim analysis of a major endpoint may be needed to justify halting, or modifying, such a study prematurely. If this criterion were to be adopted, it would have the practical advantage that the exact number of interim analyses would be of little importance, and so no fixed schedule is proposed (Peto R et al *Br J Cancer *1976; 34: 584-612).

b) evidence that might reasonably be expected to influence materially the care of people who require ICP management in ICU by clinicians who know the results of this and comparable trials.

c) Futility of enrolment.

The TSC will then decide whether or not to modify recruitment to the trial. Unless this happens, the TSC, project management group, clinical collaborators and trial office staff will remain blinded to the interim results. The conduct of the DSMC is according to the DAMOCLES principles [48].

#### Inspection of Records

Principal investigators and institutions involved in the study will permit trial related monitoring, audits, research ethics committee review and regulatory inspection(s). In the event of an audit, the investigator agrees to allow the sponsor, representatives of the sponsor or regulatory authorities direct access to all study records and source documentation.

#### Study Monitoring

The study will be monitored on behalf of the Co-Sponsors by the Trial Managers. Site staff should be available to facilitate the monitoring visits and must ensure that all required documentation is available for review.

Study initiation visits are carried out at all sites before recruitment commences at that site. Site monitoring is carried out in sites that recruit more than 10 patients throughout the duration of the trial. During these monitoring visits, the Trial Manager(s) carry out Source Data Verification of trial data, verification of informed consent forms and ensure the completeness of the Investigator Site File. Site monitoring is not be carried out routinely for sites recruiting small numbers of patients. Central quality control checks of trial data are however be carried out as described in section 6.0. Where central quality control of data identifies a problem with data collection at any site, or if the Chief Investigator and/or Co-Sponsors have concerns surrounding the quality or validity of the trial data at any site, a site monitoring visit will be conducted.

Serious breaches in the study protocol and/or Good Clinical Practice identified through trial monitoring will be notified immediately to the Co-Sponsors and appropriate corrective action will be taken and documented.

## Discussion

The Eurotherm3235Trial is the result of a Delphi exercise surveying ESICM member's views on research priorities and started in January 2009 with protocol development. This trial is therefore unique, being identified as a priority by members of a scientific society and funded, independent of industry, by the same scientific society.

The burden of bureaucracy that investigators now have to face to conduct clinical trials is larger than ever before. One particular aspect of recent legislation delayed the development of the Eurotherm3235Trial database and management of potential legislative impediment (Commission Nationale De L'informatique Et Des Libertés). This has meant that the data server(s) are now hosted in the University of Edinburgh (UoE). The database went live on April 9, 2010 and prior to this, the trial could not randomise patients outside of Edinburgh.

Detailed contracting is now necessary in all academic clinical trials. The contracts required for the Eurotherm3235Trial include:

• the financial contract between ESICM and the UoE;

• the provision of the trial database between Lincoln, ESICM and the UoE;

• clinical site agreements between the UoE and each recruiting centre (including financial agreement);

• separate contracts for the UK and international sites including Italy, Germany, Russia, Hungary and Greece, required to incorporate the Laws of each participating country. International contracts have been translated to a legal standard then similarly back-translated to ensure consistency whichtakes approximately 6 weeks;

• a service level agreement has between the Chief Investigator and the UoE for the data stored in Edinburgh.

The trial has already achieved many milestones. It is registered with the European registry of trials (http://www.controlled-trials.com ISRCTN34555414). Sponsorship has been agreed: the trial is co-sponsored by the UoE and NHS Lothian in the UK and the UoE outside the UK. Insurance for non-negligent harm has been provided by the UoE for European and Australasian centres but the associated high per-claim-deductable for USA centres has slowed progress in North America. Research ethics committee approval was obtained in Scotland and England in June 2009 and Hungary, Eire, Estonia, Russia, Italy and Germany in May-July 2010, and submissions are well advanced in Greece, Portugal and Belgium. National Institutes for Health Research Portfolio Adoption was achieved following a complex and time consuming process in the UK. This does however make the trial more attractive to UK centres. Trial documentation has been translated into various European languages including Italian, French, German, Dutch, Estonian, Russian, Hungarian, Greek, Flemish and Portuguese.

The current emphasis is on developing the recruitment infra-structure, which is ongoing. This effort required an extremely high level of input; however, the Eurotherm3235Trial is in good shape for the ongoing challenge of the recruitment phase as a result of the hard work of the Trial Coordinating Team, together with Investigators, in establishing the recruitment infrastructure. This work will continue to be of highest priority in order to maximise recruitment.

The trial is open to all ICUs with TBI patients and we encourage clinicians to visit the trial website, register an interest and complete a centre survey. The Trial Coordinating Team are available to help you with regulatory submissions.. The results of the Eurotherm3235Trial will be relevant to all those who look after patients with TBI. The trial can only be successful if clinicians and nurses from ICUs worldwide contribute. We thank the large number of Investigators who are contributing to this trial already.
